**LIST OF ABBREVIATIONS AND RELEVANT DEFINITIONS**

| **ED**  **RCT** | **Emergency Department**  **Randomized Controlled Trial** |
| --- | --- |
| **METC**  **ASA**  **QoR**  **NRS**  **VAS** | **Medical research ethics committee (MREC); in Dutch: medisch-ethische toetsingscommissie (METC)**  **American Society of Anesthesiologists**  **Quality of Recovery**  **Numeric Pain Rating scale**  **Visual Analog Scale** |
| **PENG**  **FICB**  **FNB**  **LA**  **OR** | **Pericapsular Nerve Group block**  **Fascia-iliaca Compartment Block**  **Femoral Nerve Block**  **Local Anaesthetic**  **Operating Room** |
| **(S)AE**  **SAR** | **(Serious) Adverse Event**  **Serious Adverse Reaction** |
| **SUSAR**  **LAST** | **Suspected Unexpected Serious Adverse Reaction**  **Local Anaesthetic Systemic Toxicity** |
| **AVG** | **Dutch Act on Implementation of the General Data Protection Regulation; in Dutch: Uitvoeringswet AVG** |
| **WMO** | **Medical Research Involving Human Subjects Act; in Dutch: Wet Medisch-wetenschappelijk Onderzoek met Mensen** |

**SUMMARY**

**Rationale:**

So far, literature directly comparing the different options to provide regional anaesthesia after a hip fracture is scarce, and not focussed on early administration of nerve blocks in the emergency department (ED).

**Objective**:

The aim of this study is to compare the efficacy and safety of preoperatively placed Pericapsular Nerve Group block (PENG), Fascia-Iliaca Compartment Block (FICB) and Femoral Nerve Block (FNB) for patients with hip fractures in the ED.

**Study design:**

This study is a Randomized Controlled Trial (RCT).

**Study population:**

The research population consists of adult patients (18+) with a proximal femur or neck of femur fracture.

**Intervention (if applicable)**:

Participants will receive either FNB, FICB or PENG block.

**Main study parameters/endpoints:**

The main study parameter is patient-reported QoR-15 score.

**Nature and extent of the burden and risks associated with participation, benefit and group relatedness:**

Although PENG, FICB and FNB are overall safe when performed correctly, there are some risks associated with these procedures. These risks include: bleeding (1-2% chance), infection, damage to surrounding structures, (permanent) nerve injury, and intravascular uptake of local anesthetic resulting in systemic toxicity (LAST). In addition, there is a 5-10% chance that the block provides suboptimal analgesia with the need for additional analgesics. Important to note is that PENG, FICB and FNB are all standard care in the ED. However, since all included types of regional anesthesia in the setting of traumatic femur fractures are part of well-established clinical practice, there is no additional risk for the patients participating in this study. **INTRODUCTION AND RATIONALE**

An aging population will result in a growing prevalence of hip fractures.^1,2^ Hip fractures pose an increased risk of mortality, morbidity, and functional impairment.^3^

Adequate perioperative pain reduction is of utmost importance as pain is an important factor influencing complication rates, posing a significant risk for decreased functional outcomes, prolonged time to mobilization and longer hospital stay.^4,5^ Systemic analgesia is commonly used in the pain management of patients with hip fractures, including opioids (e.g. morphine or fentanyl).^6^ However, opioids are associated with adverse events such as delirium, vomiting, pruritus and respiratory depression, which are even more common in older patients.^7,8^ Additionally, opioids are highly addictive, as illustrated by the ongoing worldwide opioid crisis.^9^

An alternative method to obtain adequate analgesia is the use of regional nerve blocks. Nerve blocks have several advantages over systemic analgesia. First, they may provide superior analgesia.^5^ Second, they contribute to a reduction in opioid use and opioid-related adverse events, and thereby decrease the risk of delirium and cognitive dysfunction.^10-12^ Previous research has shown that survival and length of hospital stay are both positively associated with the use of regional anesthesia in hip fractures.^13^ Recent guidelines therefore advise to use regional anaesthetic techniques for pain management in hip fractures.^14-16^

Various different techniques can be applied to perform regional anaesthesia for patients with hip fractures, such as the femoral nerve block (FNB) or the fascia iliaca compartment block (FICB). While FNB and FICB reduce pain in proximal femur fractures, they do not provide adequate analgesia under all circumstances.^17^ As both blocks primarily target the femoral nerve, this may be explained by inadequate blockage of the obturator nerve and/or the lateral femoral cutaneous nerve.^18-25^ More recently, the pericapsular nerve group (PENG) block has been introduced as an alternative. The PENG block, being a more cranially placed block, has the potential to target the obturator nerve better and to thereby provide better overall limb analgesia.^20,26^

So far, literature directly comparing the different options to provide regional anaesthesia after a hip fracture is scarce, and not focussed on early administration of the blocks in the emergency department (ED) before hip fracture surgery.

The aim of this study is therefore to compare the efficacy and safety of preoperatively placed PENG, FICB and FNB by assessing pain, opioid use and patient reported outcomes in patients with hip fractures presented in the ED.

# OBJECTIVES

**Primary Objective:**

To compare patient reported outcomes as measured with the QoR-15 questionnaire between patients with hip (proximal femur) fractures receiving three different pre-operative blocks in the ED: PENG block, Fascia-iliaca compartment Block or Femoral Nerve Block.

**Hypothesis:**

**H0:** There is no significant difference in the QoR-15 scores between patients receiving PENG, FICB or FNB in the ED.

**H1:** There is a significant difference in the QoR-15 scores between patients receiving PENG, FICB or FNB in the ED.

**Secondary Objective(s):**

- To compare pre-operative pain scores 15 min, 30 min, and 1 hour post-block placement in patients receiving PENG, FICB and FNB in the ED.
- To compare the amount of rescue medication, calculated as mg/hour given IV in the ED after block placement or SC/IO in the ward during the first 12 hours after block placement or until operation.
- To compare complications of block placement in patients receiving PENG, FICB and FNB in the ED in the first 24 hours after block placement.

# STUDY DESIGN

This study will be a non-blinded, multicentre Randomized Controlled Trial (RCT), conducted in the ED of the MCL and other cooperating hospitals. Patients with a confirmed proximal- or neck of femur fracture are randomized to one of three treatment arms: FICB, FNB or PENG. After randomization regional anaesthesia is provided according to a standardized protocol and pain scores are measured at fixed time intervals. Patient reported outcomes are measured with a validated (QoR-15) questionnaire either 6-8 hours after block administration or before admittance to the operating room (OR), whichever one comes first. A flowchart of the study design can be found below (*Figure 1*).

**Figure 1**. Flowchart of the study design.

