**Study design**

Hip fracture is confirmed in patient via X-ray, indication for nerve block is established and informed consent is obtained.

Patient with presumed hip fracture is presented at the ED.

Pain score and prehospital analgesics administered are obtained.

Randomization to one of three treatment arms.

Nerve Block is administered in the ED by ED clinician

The clinician/nurse continues the care process and registers study data.

*For a detailed figure on data collection, see* [*5.3 study procedures*](#_Study_procedures)*.*

Patient is admitted from ED to designated department elsewhere in the hospital.

At 6-8 hours post-block, or pre-OR (whichever one comes first), additional data are collected.

*For a detailed figure on data collection, see* [*5.3 study procedures*](#_Study_procedures)*.*

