## Randomisation, blinding and treatment allocation

Block-randomization will be performed via the REDCap randomization module on a 1:1:1 basis for every participating centre.

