As the QoR-15 questionnaire needs to be collected 6-8 hours after block administration, or before admittance to the OR (whichever one comes first), a member of the research team will visit the patient at their designated department (surgery or orthopaedics) to collect this data when 6-8 hours have passed since block administration, or pre-OR.

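### The trial is left fully open although its primary endpoint is patient-reported and partial masking of patient and QoR-15 collector looks workable

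*Protocol*

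**What the plan says.** Section 2 (Study design) sets the blinding status: "This study will be a non-blinded, multicentre Randomized Controlled Trial (RCT". It makes no exception for the patient or for whoever collects outcomes. Section 5.2 carries blinding in its heading, but its only content is "Block-randomization will be performed via the REDCap randomization module on a 1:1:1 basis for every participating centre". No masking step appears anywhere in the protocol, and no reason is given for having none.

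The Summary defines the primary endpoint: "The main study parameter is patient-reported QoR-15 score". Section 5.3 says how it is obtained: "a member of the research team will visit the patient at their designated department (surgery or orthopaedics) to collect this data", at 6–8 hours after the block or before surgery if that is sooner. The secondary pain scores at 15 minutes, 30 minutes and 1 hour are also self-reported.

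On the arms, the Summary says "Participants will receive either FNB, FICB or PENG block". There is no sham or no-block arm, and section 4.1.1 describes all three blocks as ultrasound-guided with the patient supine. In the study flowchart (Figure 1), "Nerve Block is administered in the ED by ED clinician" and "The clinician/nurse continues the care process and registers study data". The Introduction says that the PENG block "has the potential to target the obturator nerve better and to thereby provide better overall limb analgesia".

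**The concern.** A self-reported score can move with what the patient believes about the treatment received. If patients learn which block they had, any difference in expectation between arms enters the QoR-15 directly. The planned analysis cannot separate it from an effect of the block, and a larger sample would not remove it. A second, weaker route runs through the collector: someone who knows the arm and helps a patient with the form may influence the answers.

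Open trials are often unavoidable because the arms look different to the patient or because assessor and operator are the same person. Neither reason clearly applies here. Every patient receives an active injection, and the questionnaire is collected hours later in another department. The exposure to bias therefore looks avoidable in part. Section 3.4 itself expects differences between the blocks to be small, which leaves little room for a reporting bias.

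**Working it through.** **Is masking of patient and collector workable on the protocol's own description?**
- Arms: three active blocks, supine, ultrasound-guided (section 4.1.1). No arm reveals itself through the absence of an injection.
- Consent: listed ahead of randomisation in the text of Figure 1, so it can be obtained without naming the block that is later drawn.
- Place and time: the operator is in the ED. The QoR-15 is collected later on the surgical or orthopaedic ward (section 5.3).
- Access: the research team has access to the coded study files (section 9.1), and nothing limits this for the person who collects the QoR-15.
- Unmasking routes: section 5.3 and the case report form (Appendix IV) record block characteristics beyond the allocation, including landmarks and the type and amount of local anaesthetic. The injected volume is 15 ml for the femoral block and 40 ml for the other two (section 4.1.1). Hiding the allocation field alone would therefore not mask the collector.

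**Reproducing the planned size.** Inputs from section 3.4: difference 6.0, SD 10, power 0.9, alpha 0.05. Section 7 makes the test two-tailed.
- Normal approximation: n = 2 × (1.960 + 1.282)² × 10² / 6² = 58.4, so 59 per arm.
- Exact t-test: 59.35, so 60 per arm and 3 × 60 = 180, as stated. Adding 10% gives 198.

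**How sensitive is the comparison to a bias?** The size b of the shift in one arm is assumed, because the documents give none.
- Standard error of a pairwise difference: 10 × √(2/60) = 1.83 points.
- False-positive rate with no true difference: P = 1 − Φ(1.96 − b/1.83) + Φ(−1.96 − b/1.83).
- One-way ANOVA (section 7): noncentral F on 2 and 177 degrees of freedom, noncentrality 60 × [(2b/3)² + 2(b/3)²] / 100 = 0.4b².
- Power when a shift of b works against a true 6-point difference: two-sided test with a difference of 6 − b.

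| Assumed shift b | Share of the 6-point target | Pairwise false-positive rate | ANOVA false-positive rate | Power if b hides a true 6 points |
|---|---|---|---|---|
| 0 | 0 | 5.0% | 5.0% | 90.8% |
| 1 | one sixth | 8.5% | 8.1% | 78.2% |
| 2 | one third | 19.5% | 18.5% | 59.1% |
| 3 | one half | 37.6% | 37.3% | 37.6% |

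The 90.8% is the normal approximation; the t-test gives 90.3%.

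**The case against.** The open design is declared. It is neither an error nor a contradiction, and the word blinding in the heading of section 5.2 does not leave the status unstated. That is correct: the point is an avoidable weakness in a design choice, and no more.

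A reader might infer that interviewer effects feed straight into the primary endpoint. The documents do not support that. Appendix III is addressed to the patient, who is asked to check that all 15 questions are answered. Section 5.3 speaks of collecting the data and describes no interview. The collector route matters only if the patient is helped. Nor does any section say that the collector was at the block or knows the arm; the protocol only fails to prevent it.

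A reader might also infer that patients expect PENG to do better. The favourable sentence about PENG is scientific rationale, the hypothesis in section 1 has no direction, and all three blocks are described as standard care. The patient information (Appendix V) is not available for this review, so it cannot be known whether patients are told the block name or anything about its merits. A differential expectation is possible but not shown.

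Finally, masking would be incomplete. Volumes and probe positions differ, staff may mention the block, and ED pain scores are registered by staff who continue the care and may know the block. A separate collector could need extra people, and the protocol gives no staffing figures. These limits stand. They narrow what masking can achieve, but they are no reason to omit the steps that need little effort.

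**Conclusion.** The point holds as a recommended, inexpensive improvement. The protocol fixes an unqualified open design for a patient-reported primary endpoint, although its own description allows the block to be withheld from the patient and, in large part, from the collector. Patient expectation is the main route of bias and the collector's knowledge a lesser one.

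The size is unknown. The false-positive rates of 8.5%, 19.5% and 37.6% show how little bias it takes to matter against a standard error of 1.83 points. They rest on assumed shifts of 1 to 3 points placed wholly in one arm, with SD 10 and 60 evaluable patients per arm. They should not be read as the error rate this trial will have. It would also be too strong to conclude that the trial could be fully blinded.

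**What to change.** In sections 2 and 5.2, replace the unqualified statement by patient and collector masking where feasible, and do not call the trial fully blinded. Specifically:
1. State that only the operator and the treating ED staff need to know the block.
2. Do not name the allocated block to the patient before the QoR-15 is completed, and check that the patient information agrees with this.
3. Set REDCap rights so that whoever collects the QoR-15 sees neither the allocation nor any block-characteristic field (block type, landmarks, local-anaesthetic volume and dose).
4. Where existing staffing allows, have the QoR-15 collected by someone who was not present at the block.
5. Record with each QoR-15 whether the patient and the collector knew the allocation, so that residual unmasking can be reported by arm.

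The cost is protocol and patient-information wording, a change of REDCap user rights and two items on the form. Item 4 is conditional because it could otherwise require staff. The sample size stays at 180 evaluable and 198 included, and no treatment changes. The downside is the discipline asked of ED and ward staff not to name the block, and some unmasking will still occur.

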**Study design**

Hip fracture is confirmed in patient via X-ray, indication for nerve block is established and informed consent is obtained.

Patient with presumed hip fracture is presented at the ED.

Pain score and prehospital analgesics administered are obtained.

Randomization to one of three treatment arms.

Nerve Block is administered in the ED by ED clinician

The clinician/nurse continues the care process and registers study data.

*For a detailed figure on data collection, see* [*5.3 study procedures*](#_Study_procedures)*.*

Patient is admitted from ED to designated department elsewhere in the hospital.

At 6-8 hours post-block, or pre-OR (whichever one comes first), additional data are collected.

*For a detailed figure on data collection, see* [*5.3 study procedures*](#_Study_procedures)*.*

# STUDY POPULATION

## Population (base)

The research population will consist of adult patients with a femoral neck fracture or intertrochanteric femur fracture.

## Inclusion criteria

In order to be eligible to participate in this study, a subject must meet all of the following inclusion criteria:

- 18 years or older.
- proximal- or neck of femur fracture requiring surgical intervention.
- Able and willing to provide informed consent and reliably report symptoms to the research team.

## Exclusion criteria

Patients meeting any of the following criteria will be excluded from participation in this study:

- Known allergy to local anaesthetics.
- Infection at the injection-site.
- Periprosthetic fracture.
- Skin injury, local infection or recent burns hindering the use of ultrasound for ultrasound guided nerve block placement.
- Multiple fractures simultaneously.
- Pain score of < 2 (range 0 - 10) or < 20 (range 0 - 100) in rest or when moving in bed, when presented to the ED.

## Sample size calculation

Sample size was based on the primary outcome measure (QoR-15 score) and a superiority design. Following this design, an independent samples t-test was used, reasoning that one block would be superior to all others if it outperforms its best performing competitor. Based on previous research, a clinically relevant difference is determined at 6.0 points difference in QoR-15 scores.^27^ Also based on previous literature, a standard deviation of 10 is used.^28-30^ A power of 0.9 is used to minimize the chance of missing differences between the groups, as the differences in scores are likely to be small. In order to detect this difference between any of the three groups with a pre-defined p-value of 0.05, 180 patients are needed (distributed over three groups of 60). To account for 10% attrition, i.e. potential dropouts during the study process, a total of 198 patients will be included.

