# STATISTICAL ANALYSIS

Standard descriptive statistics will be used to summarize patient characteristics. Continuous data will be inspected for normality before analysis (Shapiro-Wilk), summarized with mean and standard deviation if normally distributed, or median and 25-75th centiles (Q1, Q3) if not normally distributed, and evaluated for differences with the One-Way ANOVA (if normally distributed) or Friedman Test (if not normally distributed). Categorical data will be summarized by frequency count and percentage calculations. Examination of possible associations between data will be done by Chi-Square Test or Logistic Regression. LA-type will be used as an interaction term to investigate the influence of the type of LA used. If needed, quantile regression, suitable for skewed data, will be used to identify confounders that may impact on postoperative quality of recovery scores. A two-tailed P-value <0.05 will be taken to indicate statistical significance.

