## Benefits and risks assessment, group relatedness

There is no increased risk or potential benefit for patients participating in the study, as PENG, FICB and FNB are all standard care and are currently performed in the ED. When any block is found to be superior by this study, this knowledge will however benefit the whole future population of patients with hip fractures.

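### Section 3.4's 90% power holds for one two-arm t-test; it is not guaranteed for the three-arm claims it is attached to, and Section 7's omnibus ANOVA does not identify a superior block

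*Protocol*

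**What the plan says.** Protocol Section 3.4 begins: "Sample size was based on the primary outcome measure (QoR-15 score) and a superiority design". It then says that "an independent samples t-test was used, reasoning that one block would be superior to all others if it outperforms its best performing competitor". The inputs are that "a clinically relevant difference is determined at 6.0 points difference in QoR-15 scores" and that "a standard deviation of 10 is used", with a target power of 0.9. The conclusion is: "In order to detect this difference between any of the three groups with a pre-defined p-value of 0.05, 180 patients are needed", in three arms of 60, raised to 198 for attrition.

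The hypothesis in Section 1 is global: no difference among the three blocks, against some difference. In Section 7, continuous data are to be "evaluated for differences with the One-Way ANOVA" if normal and with the Friedman test if not, at a two-tailed 0.05. Section 8.3 describes the benefit to future patients that follows "When any block is found to be superior by this study".

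**The concern.** Four parts of the protocol describe the primary comparison, and they do not describe the same one. The sizing uses one pair of arms. The sizing argument concerns a block that is better than both others. The hypothesis and the Section 7 test concern any difference among three. The expected conclusion is that one block wins.

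The step from one pair to three arms is where the power claim weakens. The best competitor is not known in advance, so showing that a block is better than both others means winning two correlated tests. When the two competitors are close, that is harder than winning one. An omnibus test has a different power again, which depends on where the third arm lies.

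What is at stake is the primary endpoint. The stated 0.90 may be more than the trial has for the claim that readers will look for, and the written test does not lead to a statement about which block is superior.

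**Working it through.** **Inputs.** Difference 6, SD 10, power 0.9, alpha 0.05 and 60 per arm come from Section 3.4. Two-sided testing comes from Section 7 and 1:1:1 allocation from Section 5.2. Equal SDs and normal scores are assumed throughout.

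**1. Reproduce the plan's figure.** For one pair, n per arm = 2(z₀.₉₇₅ + z₀.₉₀)²σ²/δ² = 2 × (1.960 + 1.282)² × 100/36 = 58.4, so 59 by the normal approximation. The exact t-test gives 59.35, so 60 per arm, and 3 × 60 = 180. At 60 per arm the noncentrality is 6/(10√(2/60)) = 3.29 and the power is 0.903. Splitting alpha over three pairs would have required 77 per arm, so the 60 contains no allowance for three comparisons.

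**2. The test in Section 7.** One-way ANOVA with 2 and 177 degrees of freedom, λ = nΣ(μᵢ − μ̄)²/σ², n = 60, largest gap fixed at 6:

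| Means | λ | Power |
|---|---|---|
| 0 / 3 / 6 | 60 × 18/100 = 10.8 | 0.839 |
| 0 / 2 / 6 | 60 × 18.67/100 = 11.2 | 0.853 |
| 0 / 1 / 6 | 60 × 20.67/100 = 12.4 | 0.888 |
| 0 / 0 / 6 | 60 × 24/100 = 14.4 | 0.931 |

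The sum of squares is smallest when the third arm is midway, so 0.839 is the minimum for a 6-point largest gap. Reaching 0.90 there needs 72 per arm.

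**3. The claim that one block beats both others.** Both two-sided 0.05 t-tests must favour the best arm. They share that arm, so their correlation is 0.5. Results at 60 per arm, from 400,000 simulated trials:

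| Means | Best beats both |
|---|---|
| 0 / 0 / 6 | 0.837 |
| −3 / 0 / 6 | 0.903 |
| −6 / 0 / 6 | 0.903 |

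The bivariate normal approximation for the first row is 0.844. If the ANOVA must also be significant, the first row becomes 0.834. With tied competitors, 0.90 needs 71 per arm.

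**4. A 6-point pair tested after a significant ANOVA.** With means 0 / 3 / 6, power for the outer pair is 0.833.

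**5. Error rates with equal means.** If three unadjusted pairwise tests were used, the chance of at least one false difference would be 12.2%. The chance of falsely finding a block that beats both others would be 1.4%. That chance rises to about 5% when two arms tie above the third (5.0% for 0 / 6 / 6).

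**The case against.** The strongest reply is that nothing was miscalculated. Section 3.4 says openly that it used a t-test and why, and 180 follows. That stands: a reader might infer an arithmetic error, and there is none.

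A second reply is that Section 3.4 compares a block with its best competitor, so the natural assumption is a 6-point lead over the runner-up. Under that assumption ANOVA power is never below 0.93, and the probability of beating both is below 0.90 only when the competitors are close. This also stands. It rules out two stronger readings: that the design simply has 83% power, and that 0.90 is too high for every claim. The 0.84 is the least favourable case. The midway configuration nevertheless belongs here, because the protocol also claims to detect 6 points between any of the arms.

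A third reply is that pairwise follow-up and multiplicity control are often left to a statistical analysis plan, which is not at hand. The hypothesis in Section 1 is global, ANOVA tests it, and Section 8.3 is a statement of benefit, not a decision rule. So the absence of a post-hoc step is not a fault in itself. What remains is a conflict within the protocol: a later plan could add contrasts, but Section 3.4 would still attach 0.90 to claims that a single t-test does not cover.

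Finally, a reader might infer a 12% false-positive rate. The protocol plans no unadjusted pairwise tests, so that figure is only the risk if they were used.

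**Conclusion.** The concern holds as a mismatch between the sizing test, the claim attached to it and the stated analysis. The 0.90 is right for one pairwise comparison. For the wider claims at 60 per arm, power lies between 0.84 and 0.93 for the ANOVA when the largest gap is 6, and between 0.84 and 0.90 for beating both competitors when the lead over the runner-up is 6. The shortfall is therefore at most about 6 to 7 percentage points, and in favourable configurations there is none. A significant ANOVA alone does not support a statement that a particular block is superior.

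These figures rest on the protocol's own difference and SD, normal scores, equal variances and 60 evaluable patients per arm. They cover the ANOVA branch only. The Friedman test named for non-normal data is a test for related samples, whereas these arms are independent groups.

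**What to change.** Keep the sample size and change two sections.

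- **Section 3.4.** Say that 0.90 is the power of a single unadjusted pairwise comparison. Give about 0.83 to 0.84 as the least favourable power under a 6-point difference, and show the more favourable configurations beside it (0.93 for the ANOVA with 0 / 0 / 6; 0.90 for beating both when the third arm is 3 or more points below the runner-up).
- **Section 7.** For QoR-15, test the omnibus hypothesis at 0.05 and, only if it is significant, the three pairwise contrasts each at 0.05. With three groups this is a closed procedure: if all means are equal the omnibus test guards the error, and if exactly two are equal only one true null pair remains. Declare a block better than both others only if both of its contrasts are significant in its favour. For non-normal data use an independent-groups equivalent, such as Kruskal-Wallis followed by pairwise rank-sum tests.

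The cost is wording and a less favourable stated power, with no extra patients. If 0.90 is wanted in the least favourable case, the alternative is 71 to 72 per arm: 213 to 216 before attrition instead of 180, or 33 to 36 more patients.
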